### Safety

At visits 2–4, safety data will be collected based on vital signs (respiratory, heart rate, and body temperature) and electrocardiography (ECG). We will request consent for the collection of blood and urine samples to assess hepatic and renal function. The blood and urine samples will be collected at 13 hospitals and stored at room temperature. After completion of sample collection, laboratory analysis will be conducted in the laboratories of hospital. The remaining samples will be destroyed after being examined. Adverse events (AEs), defined as negative or unintended clinical manifestations following treatment, will be observed and recorded throughout the trial. If an AE occurs, the clinical researcher will adopt appropriate measures to guarantee the safety of participants. If a serious AE occurs, the clinical researcher will report it to the Medical Ethics Committee and a decision will be taken whether to terminate the trial. When the patients develop to grade II or III hypertension, adverse events (AEs) will be reported to the data monitoring committee as well as the medical ethics committee. The severity and causality will be estimated by researchers.

### Data management

The researcher will collect information on participants enrolled in this study and the data will be input into a validated database which identified participants by a participant code rather than participant names. Database lock will occur once quality assurance procedures have been completed. Once data are input into the database, data validation checks will be performed via computer. The changes to the study data will be recorded. Any data required to support the protocol can be supplied on request.

The database is safeguarded against unauthorized access by established security procedures and supported by the database administrator in conjunction with any updates or changes to the database. Data for analysis is locked and cleaned according to established procedures.

A data monitoring committee will be formed, which include the corresponding author, 1 independent biostatistician, and 2 independent expert members specialized in clinical trials. The goal of the committee is to regularly review and maintain the confidentiality of the accumulating data. In addition, the committee is also formed to safeguard the interests of the participants. The committee will meet once every 3 months over the course of the trial to check the data of the trial.

### Interim analysis

An interim analysis will be performed for the primary outcome and adverse events after starting the trial for 1 year. During the interim analysis, the trial will be continued. The trial will be terminated early if clear benefit or harm of the treatment is shown after the interim analysis.

### Statistical analysis

The data analysis will be based on the principle of intention to treat (ITT), and potential missing values will be filled in using data from the last observation. Data will be presented as mean ± standard deviation, median with range, or number and percentage. Data will be analyzed using SAS 9.3 software (SAS Institute, Cary, NC, USA) using two-sided tests and a significance level of *p* < 0.025. For comparison between groups, two independent sample *T*-test (group *T*-test ) and Wilcoxon rank sum test were used for measurement data. The Pearson chi-square test or Fisher exact test was used for counting data. Wilcoxon rank sum tests were used for grade data. For intra-group comparison, paired *T*-tests or Wilcoxon symbolic rank test was used for measurement data. CMH chi-square tests were used when considering the central effect. Sub-group analyses will be conducted based on the characteristics of included participants.

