## Design and method

### Study setting

The study is a randomized, multi-center, double-blinded, non-inferiority clinical trial. The protocol for the trial was approved by the Medical Ethics Committee of Xiyuan Hospital of the Chinese Academy of Chinese Medical Sciences (2020XLA027-3) and registered in the Chinese Clinical Trial Registry (http://www.chictr.org.cn/showproj.aspx?proj=55279) with number ChiCTR2000033890 on 15 June 2020. The protocol is written in accordance with the Standard Protocol Items: Recommendations for Interventional Trials (SPIRIT), showed as Supplementary File 1 [13]. And the schedule of enrolment, interventions, and assessments is shown in Fig. 1 and the study flowchart is shown in Fig. 2.

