### Withdrawal, dropout, and discontinuation

Enrolled participants that fail to complete all the assessments of the trial, regardless of when or why, will be considered to have withdrawn. Reasons for withdrawal will be recorded on case report forms (CRFs), and data for these participants will be included in the final analysis only up to the last follow-up.

The trial can be terminated in the following cases: (1) participant(s) develop grade II or III hypertension, and other antihypertensive medicines should be added based on treatment guidelines [15], (2) no effects of the test drugs are observed during the trial, or a decision to terminate is taken (3) based on financial or management reasons or (4) by administrative authorities.

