### Sample size

The target sample size was calculated according to the decreased value of systolic blood pressure (12.9±11.8 mm Hg) observed after 8-week treatment with valsartan capsules in a randomized clinical trial [16], and the non-inferiority margin of QDG has been established as −3 mm Hg. The decreased value of QDG on systolic blood pressure was 12.0±10.5 mm Hg, which was calculated based on our clinical practice. The minimal sample size to achieve a type I error rate of *α* = 0.05 and a power of 80% (type II error rate *β* = 0.2) is 440 participants. The size was calculated using the formula:$$n=\frac{{\left({Z}_{1-\alpha }+{Z}_{1-\beta}\right)}^2\times \left({\upsigma}_1^2+{\upsigma}_2^2\right)}{{\left(\varepsilon -\delta \right)}^2}$$where σ_1_ and σ_2_ are the standard deviations of the QDG and control groups, respectively; *ε* is the mean difference between the two groups; δ is the non-inferiority margin; *α* is the type I error rate; and *β* is the type II error rate. The study will strive to enroll 550 participants to compensate for a dropout rate as high as 20%. For convenience of randomization, we will aim to recruit 552 patients.

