### Intervention

The course of treatment will last 4 weeks, and patients will be followed up for 4 additional weeks to assess any persistent effects of the drug. Participants will be examined at week 0 (baseline, visit 2), week 4 (end of treatment, visit 3), and week 8 (end of follow-up, visit 4). The QDG group will be treated with valsartan capsule simulation agent (80 mg, once daily for 4 weeks) and QDG (5 g, twice daily for 4 weeks), while the control group will be treated with valsartan capsule simulation agent (80 mg, once daily for 4 weeks) and QDG simulation agent (5 g, twice daily for 4 weeks). The drugs and simulation agents will be provided by Jiangyin Tianjiang Pharmaceutical (Jiang’yin City, China). The simulation agent will be prepared using soluble starch, colorant, and a bitter additive to achieve appearance, smell, and taste comparable to the drug. The drugs and simulation agents will be identical in outer packaging, color, shape, and flavor. The drug that patients did not take would be returned to the researcher. And no other anti-hypertension drugs should be taken during the study process.

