### Outcomes assessment

#### Primary outcome

After 4 weeks’ treatment, the decreased values of clinic systolic blood pressure and diastolic blood pressure after treatment are used as primary outcome (the difference between visits 3 and 2). Clinic blood pressure was measured using an automated sphygmomanometer (Omron, HEM-7121) in the right arm with an appropriate cuff size. The measurements were taken after the participants rested in a sitting position for 5 min, at least 1 h after the subject’s last meal, and at least 30 min after smoking or consuming caffeinated beverages. To obtain accurate data, the measurements will be conducted 3 times, and the mean value will be used as the outcome.

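### For a non-inferiority comparison the article names only an intention-to-treat analysis with last-observation imputation; if loss or non-adherence is similar in both arms, this dilutes a true deficit and makes the claim easier to reach

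*Protocol article*

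**What the plan says.** The Study setting section states the aim: "The study is a randomized, multi-center, double-blinded, non-inferiority clinical trial". The Sample size section sets the margin at −3 mm Hg for the fall in systolic pressure.

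The Statistical analysis section gives one analysis basis, "The data analysis will be based on the principle of intention to treat (ITT"), and one rule for gaps: "potential missing values will be filled in using data from the last observation". Under Withdrawal, dropout, and discontinuation, for people who leave early, "data for these participants will be included in the final analysis only up to the last follow-up". No per-protocol or on-treatment set is named anywhere in the article.

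Three other statements bear on the point:

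- Visits (Intervention): the examinations fall at weeks 0, 4 and 8, numbered visits 2, 3 and 4. The primary outcome spans the first two of these; the falls in pressure "are used as primary outcome (the difference between visits 3 and 2"). No visit lies between them.
- Loss (Sample size): "The study will strive to enroll 550 participants to compensate for a dropout rate as high as 20"%.
- Adherence (Intervention): "The drug that patients did not take would be returned to the researcher".

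**The concern.** In a superiority trial, dilution under intention to treat is usually conservative. In a non-inferiority trial it can work the other way. Participants who take neither drug show no drug difference, so if they are similarly common in both arms the observed difference moves towards zero and away from −3 mm Hg.

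The article makes one route concrete. With no visit between week 0 and week 4, the last observation for anyone who misses visit 3 is baseline. The primary change is then entered as zero, whichever drug was assigned. A second route, non-adherence with a visit 3 reading still taken, would remain if the imputation rule were replaced.

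At stake is the error rate of the main claim: a QDG that is worse by the full margin in people who take it could be called non-inferior more often than the nominal level allows.

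**Working it through.** **The plan's own figures.** The dropout step reproduces: 440/0.80 = 550, raised to 552, or 276 per arm. The 440 itself does not follow from the printed formula and inputs: one-sided 0.05 with a difference of 0.9 gives 350 per arm, 700 in total. That is a separate matter; the check below uses only the 276 per arm.

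**Inputs** (Sample size section unless noted)
- SDs 10.5 (QDG) and 11.8 (valsartan); variance sum 110.25 + 139.24 = 249.49.
- SE of the difference = √(249.49/276) = 0.951 mm Hg.
- Margin −3 mm Hg; planned difference 12.0 − 12.9 = −0.9 mm Hg.
- Level: α = 0.05, used one-sided in the formula. The Statistical analysis section instead gives two-sided tests at 0.025, which read literally is 0.0125 per tail. Because these differ, three one-sided levels are shown.
- Assumed: a share f of each arm contributes no drug difference (5%, 10%, 20%). The article gives no non-adherence rate; 20% is its dropout allowance.
- Assumed: non-inferiority is claimed when the lower confidence limit lies above −3 mm Hg.

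**False-claim rate.** Let the true deficit among adherent participants be exactly 3 mm Hg. The expected observed difference is −3(1 − f), so

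rate = Φ( 3f/SE − z ).

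For f = 0.20 at one-sided 0.025: 3 × 0.20/0.951 = 0.631, and Φ(0.631 − 1.960) = 0.092.

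| f | expected difference (mm Hg) | one-sided 0.0125 | 0.025 | 0.05 |
|---|---|---|---|---|
| 5% | −2.85 | 1.9% | 3.6% | 6.8% |
| 10% | −2.70 | 2.7% | 5.0% | 9.2% |
| 20% | −2.40 | 5.4% | 9.2% | 15.5% |

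**Cross-check with baseline carried forward.** Take a valsartan fall of 12.9 and a QDG fall of 9.9, and give 20% of each arm a change of exactly zero, with the mixture variance. The SE becomes 0.936 and the rates 5.5%, 9.4% and 15.8%, close to the last row.

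**Partial dilution.** If the 20% keep half the drug difference, the expected difference is −3 × 0.90 = −2.70, and the rate at 0.025 is 5.0%.

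**Unequal loss, zero change carried forward.**
- 10% lost on valsartan, 13% on QDG: 9.9 × 0.87 − 12.9 × 0.90 = 8.613 − 11.61 = −3.0. No dilution.
- 10% and 15%: 9.9 × 0.85 − 11.61 = 8.415 − 11.61 = −3.2. The bias now runs against QDG.

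**The case against.** A reader might infer that the plan rules out a per-protocol analysis and commits the conclusion to intention to treat alone, with a bias that always favours QDG. The article does not support that reading.

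- **It excludes nothing.** Secondary analysis sets are commonly left to an analysis plan or full protocol, and the Data Availability section says a full protocol exists. This stands as a limit: the point concerns what the article gives a role in the conclusion. It does not remove the point, because the basis the article does state, with its imputation rule and visit schedule, can by itself dilute the comparison.
- **The direction is not fixed.** The unequal-loss figures show that a few percentage points more loss on QDG cancel or reverse the dilution, and a less effective drug could plausibly lose more people. This stands.
- **The 20% is a dropout allowance, not a non-adherence rate.** Much of its effect runs through baseline carried forward. What would remain after a better imputation rule cannot be sized from the article. This stands.
- **The word false depends on the question asked.** For the effect of assignment, a diluted deficit of 2.4 mm Hg lies inside the margin, so a claim would not be an error. The rates above refer to the effect in adherent participants. This is fair, and it is a reason to report both analyses.
- **A per-protocol set has its own selection bias.** This too stands. The Withdrawal, dropout, and discontinuation section foresees added antihypertensives after progression to a higher grade. If those are mainly QDG failures, excluding them would favour QDG.

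**Conclusion.** The concern holds in a conditional form. For a non-inferiority comparison the article names only intention to treat with last-observation imputation. When loss or non-adherence is similar in the two arms, that basis favours the claim. At the article's own 20% allowance, a deficit equal to the margin among adherent participants would pass about 5.4% of the time at one-sided 0.0125, 9.2% at 0.025 and 15.5% at 0.05. On any of these levels that is roughly three to four times nominal. At an assumed 5% the inflation is small.

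These sizes rest on equal shares in both arms, no drug difference at all in the affected participants, and the SDs in the Sample size section. They illustrate sensitivity and do not predict what this trial's error rate will be.

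**What to change.** Keep intention to treat, and add a per-protocol analysis of the visit 3 minus visit 2 change. Fix the set and the returned-drug threshold before unblinding. The Trial status section says the trial is already in data analysis, so if that is no longer possible, label the analysis post hoc.

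Report both confidence intervals against −3 mm Hg, and call non-inferiority robust only if the two agree. Do not simply drop participants given another antihypertensive; show how the result changes under different ways of handling them.

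No new patients or visits are needed. The article says that unused drug comes back but not that it is counted, so whether the records support a threshold must be confirmed.

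The cost is precision. With 20% excluded, about 220 per arm remain (276 × 0.80 = 220.8), and the SE rises from 0.95 to √(249.49/220) = 1.06 mm Hg. At the planned −0.9 mm Hg difference, power is Φ(2.1/SE − z). It falls from about 60% to 50% at one-sided 0.025, and from 71% to 63% at 0.05. Requiring agreement between the two analyses is therefore a real cost. Power is already below 80% with all 276 per arm, because the planned total does not follow from the printed formula.

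### With no blood pressure scheduled between baseline and week 4, last-observation filling is in effect baseline carried forward, and it favours non-inferiority when dropout is similar in both arms or higher on control

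*Protocol article*

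**What the plan says.** The Study setting section of the protocol article gives the design: "The study is a randomized, multi-center, double-blinded, non-inferiority clinical trial". The Statistical analysis section analyses by intention to treat and adds that "potential missing values will be filled in using data from the last observation". The Intervention section fixes the visits: "Participants will be examined at week 0 (baseline, visit 2), week 4 (end of treatment, visit 3), and week 8 (end of follow-up, visit 4"). Under Primary outcome, the falls in clinic systolic and diastolic pressure "are used as primary outcome (the difference between visits 3 and 2").

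Two other places bear on the point. The Withdrawal, dropout, and discontinuation section counts as withdrawn anyone who does not complete every assessment, and says that "data for these participants will be included in the final analysis only up to the last follow-up". The Sample size section enlarges recruitment "to compensate for a dropout rate as high as 20"%, as one overall rate with no split by arm.

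**The concern.** Read together, these sections leave the filling rule almost nothing to carry forward. The only scheduled blood pressure before the week-4 endpoint is the baseline value. For a participant with no week-4 reading, the filled value is baseline and the change is zero, unless an unscheduled reading exists.

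In a superiority trial, identical zeros in both arms usually work against the sponsor's claim. In a non-inferiority trial, a smaller difference between arms is movement toward success. If QDG is truly worse by the margin and both arms lose similar proportions, the analysis sees a smaller deficit than the one that exists on treatment, so the chance of wrongly declaring non-inferiority exceeds its nominal level. Because this is the stated rule for the primary outcome, the main conclusion of the trial depends on it.

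The rule has a second effect at week 8. A participant seen at week 4 but not at week 8 has an end-of-treatment value carried into the off-treatment follow-up, whose purpose is to see whether the effect lasts. If the effect wanes after treatment stops, persistence is overstated. This concerns secondary outcomes and is not quantified here.

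**Working it through.** **Inputs from the Sample size section.** Control fall: "decreased value of systolic blood pressure (12.9±11.8 mm Hg"). SD of the QDG fall: 10.5 mm Hg. Margin: −3 mm Hg. Dropout: up to 20%. Group size is 276 per arm (Abstract).

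**The plan's own figure.** The dropout allowance reproduces: 440 / (1 − 0.20) = 550. The 440 itself does not follow from the stated inputs, which give 350 per arm at one-sided 5%. That is a separate matter and is not used below.

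**Assumptions.** The true difference sits at the margin, so QDG falls by 12.9 − 3 = 9.9 mm Hg. Dropouts would have responded like completers. Every participant missing week 4 is filled with baseline.

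**Formulas.** With dropout d in an arm whose mean fall is m and SD is s:

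- mean after filling = (1 − d) × m
- variance after filling = (1 − d) × s² + d(1 − d) × m²
- SE = √[(sum of the two variances) / 276]
- chance of declaring non-inferiority = Φ[(expected difference + 3) / SE − z]

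**No dropout.** SE = √[(10.5² + 11.8²) / 276] = 0.951. The expected difference is −3, so the error equals its nominal level.

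**Equal dropout of 20%.**

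- Expected difference = 0.8 × (−3) = −2.40
- QDG variance = 0.8 × 110.25 + 0.16 × 98.01 = 103.88
- Control variance = 0.8 × 139.24 + 0.16 × 166.41 = 138.02
- SE = √(241.90 / 276) = 0.936
- One-sided 2.5%: Φ(0.60 / 0.936 − 1.960) = 9.4%
- One-sided 1.25%: Φ(0.60 / 0.936 − 2.241) = 5.5%

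**Range over equal dropout.**

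| Dropout in each arm | Expected difference (mm Hg) | SE | Error at one-sided 2.5% | Error at one-sided 1.25% |
|---|---|---|---|---|
| 0% | −3.00 | 0.951 | 2.5% | 1.25% |
| 5% | −2.85 | 0.951 | 3.6% | 1.9% |
| 10% | −2.70 | 0.949 | 5.0% | 2.7% |
| 20% | −2.40 | 0.936 | 9.4% | 5.5% |

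The 1.25% column is the literal reading of the Statistical analysis section (two-sided tests at p < 0.025). At one-sided 5%, the alpha in the sample size formula, 20% dropout gives 15.8%. Simulation of 20,000 trials at 20% dropout gave 9.4% at one-sided 2.5% and 16.0% at one-sided 5%.

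**Unequal dropout, one-sided 2.5%.**

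- QDG 15%, control 25%: difference = 0.85 × 9.9 − 0.75 × 12.9 = −1.26; error 46%.
- QDG 25%, control 15%: difference = 0.75 × 9.9 − 0.85 × 12.9 = −3.54; error 0.6%.
- Break-even: the difference stays at −3 when QDG dropout × 9.9 = control dropout × 12.9, a ratio of 12.9 / 9.9 = 1.30 (for example 22.6% against 17.4%). Above that ratio the bias runs against QDG.

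**At the planning difference.** With true falls of 12.0 and 12.9 and one-sided 2.5%, zero-filling 20% of each arm raises the chance of declaring non-inferiority from 59.8% (276 per arm, none missing) to 67.0%. Losing data appears to add power.

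**The case against.** Several stronger readings are tempting, and the case against them is sound.

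- **The rule always favours non-inferiority.** It does not. The direction depends on the split of dropout between arms, which the article does not give. If QDG really is inferior, withdrawal for rising pressure could be more frequent on QDG, and beyond the 1.3 ratio the bias reverses.
- **The rule erases deterioration.** The text says last observation, not last scheduled visit. Recognising progression to grade II or III hypertension requires a reading, and that reading could be the value carried forward. The article does not say whether unscheduled readings count, so loss of this information is possible but not established.
- **One in five will lack a week-4 value.** The 20% is a ceiling, and a participant who misses only week 8 counts as withdrawn although the primary endpoint was observed. Missingness at week 4 may be well below 20%.
- **The inflated figure is a type I error on any view.** It is measured against the difference that would have been seen had dropouts responded like completers. If they stop treatment and return to baseline pressure, zero is close to their true value, and the intention-to-treat difference is itself about −2.4.
- **No per-protocol or sensitivity analysis is named.** This is a condensed article; such analyses may stand in the full protocol or the analysis plan, so their absence here is no fault.

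Two practical objections also have weight. A repeated-measures model gains no post-baseline information for participants missing both visits. And the Trial status section says that data analysis is already under way.

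These points limit the direction and size of the problem. They do not remove it: the rule is stated, the schedule makes it baseline carried forward for most participants missing week 4, and the article does not justify the assumption that such participants are unchanged.

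**Conclusion.** The point holds in conditional form. For the primary outcome, the stated rule normally assigns zero change to participants without a week-4 value. With similar dropout in both arms, or more on control, this moves a true inferiority toward zero and raises the chance of a false non-inferiority conclusion. Under equal dropout, the rise is small at 5% and close to fourfold at the planned ceiling (2.5% to 9.4%). With the true effect and the 20% average dropout held fixed, shifting the split by five points per arm in either direction moves the error from 0.6% to 46%. That sensitivity is itself a reason not to rest the primary conclusion on this rule.

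The sizes rest on the protocol's SDs, a control fall of 12.9 mm Hg that the article takes from 8 weeks of treatment, dropouts responding like completers, and no unscheduled readings. The shrinkage under equal dropout, a factor of (1 − d), does not depend on the control fall; the break-even ratio does.

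**What to change.** 1. Replace last-observation filling for the primary outcome with multiple imputation by arm, using baseline blood pressure, site and any week-8 value, or with a likelihood-based repeated-measures model. For participants missing both later visits, either method relies on baseline data and on others in the same arm; that assumption should be stated.
2. Add a sensitivity analysis that imputes missing QDG-arm changes under the non-inferiority null, that is, with falls 3 mm Hg smaller.
3. State that any blood pressure recorded at withdrawal is used in the analysis.
4. Do not carry week-4 values into week 8; handle the follow-up outcomes by the method chosen in step 1.

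Report week-4 missingness by arm, since the direction of the bias depends on it. No new data are needed. The cost is modest programming and a slightly wider confidence interval. As analysis has begun, the change should be documented with its date. If treatment codes have already been opened, report the new analysis beside the planned one and label it as a departure from the plan.

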### Randomization and blinding

Participants will be randomized in a 1:1 ratio to the QDG or control group using a computer-generated, site-stratified, block randomization schedule. The study drugs will be labeled with sequential randomization numbers, and the participant will be assigned the lowest number available at each hospital. All participants, care providers, and attending physicians will be blinded to the assignment until the trial is finished. The trial-group assignment will be concealed from all participants, clinicians, and investigators throughout the trial. To ensure blinding, randomization sequences will be generated by statisticians and then kept in identical, opaque, sealed, sequentially numbered envelopes. Only the trial’s pharmacist has access to the randomization list.

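### The tests and level fixed in Statistical analysis do not test non-inferiority against −3 mm Hg, and the level conflicts with the alpha used for sizing

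*Protocol article*

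**What the plan says.** Study setting gives the objective: "The study is a randomized, multi-center, double-blinded, non-inferiority clinical trial". Sample size adds that "the non-inferiority margin of QDG has been established as −3 mm Hg". It applies a non-inferiority formula with Z at 1−α and "type I error rate of *α* = 0.05 and a power of 80"%, so the alpha as written is one-sided 5%.

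Statistical analysis is one general paragraph covering all outcomes. It calls for analysis "using two-sided tests and a significance level of *p* < 0.025". For between-group comparisons, "two independent sample *T*-test (group *T*-test ) and Wilcoxon rank sum test were used for measurement data". It does not mention the −3 mm Hg margin, a confidence interval or bound, or a null hypothesis, and it gives no separate rule for the primary outcome.

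Primary outcome names the week-4 reductions in both clinic SBP and clinic DBP. The only margin given is the one in Sample size, where every input is systolic. Trial status reports that recruitment ended in December 2021 and that the trial is in data analysis.

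**The concern.** Two things do not fit together.

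The first is the hypothesis. A non-inferiority claim needs the null that QDG's reduction falls short of valsartan's by 3 mm Hg or more to be rejected. An ordinary two-sided t-test or Wilcoxon test addresses a null of no difference. Failing to reject that null does not show non-inferiority, and rejecting it does not show a deficit beyond the margin. A rank sum p-value also supplies no limit on a mean difference to set against −3.

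The second is the level. Sizing uses 5% in one tail. The analysis, read literally, uses 1.25% in each tail. Neither section refers to the other.

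At stake is whether the document contains a usable rule for its main claim, and whether the same data would pass or fail depending on which level is applied.

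**Working it through.** **Inputs, all from Sample size unless noted.** Control reduction 12.9, SD 11.8; QDG reduction 12.0, SD 10.5; so ε = 12.0 − 12.9 = −0.9. Margin δ = −3. Target power 80%. Allocation is 1:1 (Randomization and blinding). Planned enrolment is 552, or 276 per arm. The stated minimum of 440 is 220 per arm.

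**The plan's own figure.** The sum of variances is 10.5² + 11.8² = 110.25 + 139.24 = 249.49, and (ε − δ)² = 2.1² = 4.41. At one-sided 0.05 the formula gives n = (1.645 + 0.842)² × 249.49 / 4.41 = 349.8, so 350 per arm and 700 in total. The stated 440 does not follow. That is a separate defect and adds no weight here, but it bears on what 0.025 means: one-sided 0.025 with ε = 0 gives 218 per arm, 436 in total, which is close to 440. The dropout step, 440 / 0.8 = 550, does reproduce.

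**What the level changes.** SE = √(249.49 / n per arm), which is 0.951 at 276 and 1.065 at 220. Power against −3 is Φ(2.1/SE − z). The observed difference must exceed −3 + z × SE to pass.

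| Level applied to the margin | z | n per arm for 80% | Power at 276 | Power at 220 | Pass mark at 276 |
|---|---|---|---|---|---|
| One-sided 0.05 (Sample size as written) | 1.645 | 350 | 71% | 63% | −1.44 |
| One-sided 0.025 (two-sided 95% interval) | 1.960 | 445 | 60% | 50% | −1.14 |
| One-sided 0.0125 (two-sided 0.025 taken literally) | 2.241 | 538 | 49% | 39% | −0.87 |

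The pass marks are −3 + 1.564, −3 + 1.863 and −3 + 2.131. An observed difference of −1.0 mm Hg would pass at the first two levels and fail at the third.

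**Illustration of the wrong null.** Suppose non-significance in a two-sided zero-difference test at 0.025 were taken as non-inferiority. Nothing in the article says it will be. The critical difference is 2.241 × SE, or 2.13 at 276 per arm and 2.39 at 220. With a true difference of exactly −3, the chance of a non-significant result is Φ((2.131 − 3)/0.951) = 18% at 276 and Φ((2.387 − 3)/1.065) = 28% at 220. The rate rises as the sample shrinks, so such a rule would reward imprecision.

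**The case against.** The strongest reply is that the paragraph is a generic list of tests for all outcomes and never writes out a null. A two-sample t statistic can be set against −3, a two-sided interval is the usual vehicle for a non-inferiority bound, and the decision rule may stand in an analysis plan that is not shown. This stands in part. The zero null is inferred from the default form of the named tests, and the lack of a confidence-bound rule would not by itself be a finding. But the article is not silent. It fixes sidedness, level and tests, and in their ordinary form these do not serve the declared objective.

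A reader might infer that the trial will declare non-inferiority whenever p ≥ 0.025, and so runs an 18% to 28% false-positive rate. The document does not support that, because it nowhere equates non-significance with non-inferiority. If 0.0125 per tail were applied to a bound at −3, the test would be stricter than the sizing alpha. It would cost power and would not inflate error.

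The level may also be a slip for one-sided 0.025, as the near-match of 436 to 440 suggests. It could be 0.05 split over SBP and DBP, or an allowance for the interim analysis, but no split or adjustment is stated. None of these readings agrees with the printed α = 0.05 and Z at 1−α, so the contradiction remains.

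**Conclusion.** The point holds in this form: the between-group tests fixed for continuous outcomes do not, in their ordinary form, test non-inferiority against −3 mm Hg, and the stated level contradicts the sizing alpha with nothing to reconcile them. It must be fixed, because the main claim depends on it.

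On the plan's means and SDs, the gap between one-sided 0.05 and 0.0125 moves power at 276 per arm from 71% to 49% and the required size from 350 to 538 per arm. These figures assume the normal approximation in the plan's own formula and that the margin is what gets tested. The intended meaning of 0.025 cannot be settled from the article.

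**What to change.** - **Decision rule.** For SBP, estimate the QDG minus control difference in reduction with a two-sided 95% confidence interval. Declare non-inferiority only if the lower limit is above −3 mm Hg. Keep the Wilcoxon test as a sensitivity analysis.
- **One level.** State one-sided 0.025 in both Sample size and Statistical analysis.
- **Power.** Restate it on the sizing inputs: about 60% at 276 per arm and 50% at 220 per arm. Reaching 80% would need 445 per arm, 890 in total, against 552 planned.
- **DBP.** Either give it a justified margin and a decision rule, or make it secondary.
- **Timing.** Date the change and disclose whether it was made before or after unblinding. The article does not show whether the blind still holds.

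The cost is wording and a restated power, with no new data to collect. The restated power is a real price: recruitment has closed, so the shortfall can be reported but not repaired by a wording change.
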